### 5.3.2 Period before inclusion

In this study, there is no pre-inclusion phase. All that occurs ahead of inclusion concerns diagnosis of COVID-19. The nasopharyngeal test shall be carried out in accordance with current recommendations. No examinations, which could not be justified by the person's clinical condition, shall be carried out.

People presenting with signs or symptoms resembling COVID 19 and not having immediate hospitalisation criteria may benefit from a SARS-CoV-2 nasopharyngeal test, upon request:

- *Outside the home*: in all places where the test shall be held at the time of the trial commencing: A&E departments of hospitals or Bordeaux clinics and specific SARS-CoV-2 screening centres, which have been identified earlier.
- *At home and at nursing homes*: the mobile medical teams shall be available for all requests to attend the home address and carry out a nasopharyngeal sample, at the request of the person concerned and subject to the indication that such a sample complies with those recommendations in effect.

People who would benefit from a nasopharyngeal swab shall be informed of the existence of the trial. They shall be sent a notice informing them of what will occur if the test is positive, as well as, if they so wish, the trial information notice. If they are in an emergency department, following appraisal by the clinician, they shall then return home pending results of the test, or shall remain under observation.

During this period when the person has not yet been included, the usual examinations may be decided upon by the medical team taking care of the person in the context of the emergency services (e.g. blood electrolytes in the case of diarrhoea, ECG in the case of cardiovascular risk factors, etc.). Such examinations shall not form part of examinations linked to the trial, but their results could be used while deciding upon inclusion (please see the non-inclusion criteria, paragraph **Erreur ! Source du renvoi introuvable.**).

### 5.3.3 Inclusion (Day 0)

If the test is positive, the process leading to inclusion and inclusion itself shall take place: At the outpatient COVID-19 screening unit or in A&E, if the person is still there at the time of the results becoming available; by visit by the mobile medical team to the home or Nursing Home, if the person has returned home or lives in the Nursing Home and agrees to being seen by the team.

The test result shall be explained to the person, who shall be invited to participate in the trial. If the person is interested, the conditions for inclusion shall be checked with him/her (including the review of all treatments in progress, a systematic ECG and recourse to cardiological opinion or the on-call cardiologist for the trial for persons on each occasion that it is appropriate).

If the criteria for inclusion have been met and there is no criterion for non-inclusion, all the questions on the trial shall be answered and they shall be asked whether they agree to participate. If they agree, they are to sign with informed consent and are to be included.

After signing the consent, the inclusion visit shall include:

- Physical examination
- Pulse oxygen saturation (SpO2)
- Blood sample
- Randomisation

- Drug delivery
- Advice

Participants are to receive a document explaining what they must do in the event of symptoms suggesting a worsening of the disease or any side-effect of the drug. During the inclusion visit, particular attention is to be drawn to the living conditions of solitary people, their environment in matters of food and access to drugs other than those delivered in the context of the trial and their ability to gain access to the telephone. In the event of any problem with one of these points, suitable solutions are to be found [SDPM].

People with a QTc between 460ms and 500ms upon inclusion, or any other risk factor requiring cardiological opinion before a decision on inclusion, shall be referred to a 6 lead ECG (Kardia Mobile 6L from AliveCor; CE N°72133041) daily monitoring and shall receive the necessary advice on its functioning during the inclusion visit. This user-friendly device allows transmission of the ECG results and remote reading by the research cardiologist for the trial.

#### 5.3.4 Remote monitoring of the ECG and consideration of the blood electrolytes for inclusion

- People in receipt of an ECG device are to take a reading 3-4 hours after the morning treatment intake on Day 1, then daily 3-4 hours after it up to Day 7. The ECG shall be transmitted remotely. The ECG shall be read directly by the on-call cardiologist. In the event of any anomaly, requiring a stop to the trial's drug, the person shall be informed by telephone and receive a visit from the mobile team.

The device shall be recovered by the mobile team on Day 7.

- The kalaemia dosed on the inclusion sample shall be made available to the researchers on the same day of inclusion. In the event of severe hypokalaemia, the researcher shall contact the attending physician for corrective measures. If the confirmed figure indicates the trial drug should be interrupted, provisions shall be made by telephone with the person, the attending physician and the mobile team, so that the decision can be enacted immediately.

#### 5.3.5 Remote visits (Days 1, 3, 5, 9 and 12)

- Remote visits shall be carried out by means of the web software allowing video contact, if the participant has an internet connection and the possibility of using it in the appropriate manner; or by telephone if the opposite applies. If the person cannot be connected, the mobile team shall be activated.
- Such visits are to be standardised and refer to:
  - Clinical condition (including the recording of undesired effects)
  - Taking of the drugs (trial drugs and concomitant treatments)
  - Carrying out of self-tests for the immunological sub-study (if applicable)
  - Mental state
  - Advice

#### 5.3.6 Face-to-face visits (Day 7 and Day 14)

- Face-to-face visits shall be carried out in the participant's home by the trial's mobile team.
- Face-to-face visits are to consist of:
  - Interview and clinical examination (including the recording of undesired effects)
  - Taking of drugs
  - SpO2
  - Blood sampling
  - Nasopharyngeal swab for SARS-CoV2 RT-PCR
  - Advice

#### 5.3.7 Out of phase contacts during the trial

When any participant calls the telephone number of the trial's point of contact at unscheduled times:

- If there are suspicions that the illness requires a face-to-face appraisal, the mobile team will ensure that a home visit occurs rapidly. This visit could be carried out by the attending physician, the trial's mobile team, or any other health worker authorised to perform home visits.
- If there are suspicions that the illness requires urgent hospitalisation, the team is to contact the emergency services to organise the transfer to hospital [SDPM].

#### 5.3.8 Visit at the end of the trial (Day 28 or later)

- This is to take place:
  - On Day 28 for patients never hospitalised

- 7 days after the date of discharge from hospital if not
- The visit at the end of the trial shall be carried out by means of the web software allowing video contact, if the participant has an internet connection available and is capable of using it in the appropriate manner; or by telephone if the opposite applies.
- The visit at the end of the trial shall be devoted to:
  - Clinical condition (including the recording of undesired effects)
  - Taking of drugs
  - Mental state
  - Discussion on the progress of the patients' convalescence
  - Advice on the remaining days of convalescence
  - Information on receipt of the trial results

### 5.3.9 Changes to scheduled visits

With consideration to the tense context in which this study could occur, the trial's team has identified, during its risk appraisal, the risk that the workload linked with the epidemic and the changes in stocks of protection equipment and tests would cause changes in the schedule.

The schedule of home visits could be adapted, without calling into question the quality of the medical follow-up of people participating in the trial. The possible scenarios are as follows:

- The visits on Day 7 and Day 14 could be replaced by remote visits for people available by telephone and whose changes are clinically reassuring. The corresponding samples would therefore be omitted. If visits need to be limited, Day 7 visits shall be maintained as a priority over Day 14.
- The nasopharyngeal tests of Day 14 could be omitted for people, who had tested negative on Day 7.
- Movement of people to the outpatient diagnostic centre of the CHU de Bordeaux (Pellegrin site) arranged for this purpose for the Day 14 visit could be envisaged under three conditions: (i) confinement of the population has been implemented; (ii) these people are prepared to go out and make the visit; (iii) the prevention instructions (wearing of masks, social distancing, transport using personal vehicles) are observed. In such cases, transport could be organised by the trial's mobile teams.

Potential changes to the schedule shall be strictly framed and submitted to the SAB.

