#### 4.3.2 Secondary criteria

- Hospitalisation proportion and its causes between Day 0 and Day 28 within each group
- Proportion of deaths and their causes between Day 0 and Day 28 within each group
- Intensive care hospitalisation proportion and its causes between Day 0 and Day 28 within each group

---

 Currently, the following criteria are being proposed: SpO2 < 92% in ambient air or 4% reduction in SpO2 since inclusion; respiratory rate > 30 min; heart rate > 130/min; systolic blood pressure < 90 mmHg or diastolic < 60 mmHg; other parameters indicating hospitalisation, in the judgement of the attending physician (for example, unexplained fall, severe digestive problems, reoccurrence or persistent fever > 38.5°C etc.)

- Proportion of patients with a reversion of SARS-CoV2 RT-PCR on a nasopharyngeal swab on Day 7 and Day 14, in each group
- Proportion of patients with a loss of autonomy evaluated by ADLs and IADLs on Day 14 and Day 28
- Changes in CBC, inflammatory markers (please see paragraph **Erreur ! Source du renvoi introuvable.**) and immunological markers (please see paragraph **Erreur ! Source du renvoi introuvable.**) from Day 0 to Day 7 and Day 14 in each group
- Number and proportion of adverse events of grades 1, 2, 3, 4 between Day 0 and Day 14 in each group
- Number and proportion of adverse reactions of grades 1, 2, 3, 4 between Day 0 and Day 14 in each group
- Plasma trough concentration of experimental drugs in the study on Day 7
- Acceptability of the treatment

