### 6.3.6 Secondary endpoints

The analyses on the secondary endpoints will be performed on intention-to-treat on available data, except for safety analysis.

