### 6.3.7 Safety analysis

The analysis will be performed on participants having taken at least one dose of randomisation treatment on available data, from D0 to D14 and D28.

Adverse events will be described through SOC and PT levels of MedDRA classification (last version at time of database freezing).

The incidence of adverse events will be described in terms of nature, causality, severity, intensity.

The incidence of adverse events related to randomisation treatment discontinuation or dosage modification will be described and compared between arms.

Safety analysis will be performed in compliance with the recommendations of the Consort Statement on harm.

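### D7 and D14 samples may be dropped only for participants who are doing well, while sample-based endpoints are analysed on available data, so those comparisons can be biased in either direction

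*Protocol*

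**What the plan says.** Section 5.3.9 foresees shortages of staff, protective equipment and tests. Its first contingency reads: "The visits on Day 7 and Day 14 could be replaced by remote visits for people available by telephone and whose changes are clinically reassuring". It continues: "The corresponding samples would therefore be omitted". Two limits are attached: "If visits need to be limited, Day 7 visits shall be maintained as a priority over Day 14" and "Potential changes to the schedule shall be strictly framed and submitted to the SAB". Neither sets an analysis rule.

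The lost samples carry named endpoints. Section 4.3.2 lists "Proportion of patients with a reversion of SARS-CoV2 RT-PCR on a nasopharyngeal swab on Day 7 and Day 14, in each group", together with changes in CBC and inflammatory markers to D7 and D14 and the D7 trough drug concentration. The same blood draws provide creatinine, potassium, CPK and transaminases (section 5.3.10.2), and section 5.4.3.1 requires biological as well as clinical adverse events to be recorded.

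On analysis, section 6.3.6 states: "The analyses on the secondary endpoints will be performed on intention-to-treat on available data, except for safety analysis". Section 6.3.7 states: "The analysis will be performed on participants having taken at least one dose of randomisation treatment on available data". The opening of section 6 defines available data as leaving missing values out. It also defines worst-case and inverse probability weighting procedures, but section 6.3.4 assigns these only to the primary endpoint.

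**The concern.** Whether a sample exists would depend on how the participant is doing at D7 or D14. That is partly a result of treatment, and in an open-label trial it may be judged with the arm known. An effective drug would move more people into the group that is not sampled. The available-data comparison then sets differently selected subsets of the two arms against each other.

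At stake are the conclusions on viral clearance, inflammatory markers and blood counts. Laboratory safety is also exposed: if rates are taken over everyone treated, an unsampled person stays in the denominator with no chance of a recorded laboratory event, and the arm with more unsampled people looks safer.

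**Working it through.** **Inputs.** The protocol gives no effect size or event rate for sample-based endpoints, so there is no plan figure for them to reproduce. The 169 per arm comes from section 6.2.1. It fits the stated 80% power: simulating the three futility looks and then the final test, for 25% against 12.5%, gives 80.5% if the final one-sided alpha is 0.025 (an assumption). All inputs below are assumptions.

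**Continuous marker.** Severity S is N(0,1) on control and N(-0.5,1) on drug. The marker has unit residual-plus-signal variance and correlation r = 0.5 or 0.8 with S. A participant is reassuring if S lies below the control 50th (or 70th) percentile, and a fraction w of reassuring participants goes unsampled. The available-data difference is r × D, where D is the difference in mean S among those sampled. The true value is r × 0.5 = 0.25 or 0.40 SD.

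With 50% of controls reassuring (69% on drug), mean S is:
- Control: -0.798 if reassuring, +0.798 if not.
- Drug: -1.009 if reassuring, +0.641 if not.

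All skipped (w = 1): D = 0.798 - 0.641 = 0.157, giving 0.08 to 0.13 SD, with about 84 and 52 sampled.

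Half skipped (w = 0.5):
- Control mean = (0.25 × -0.798 + 0.5 × 0.798) / 0.75 = 0.266.
- Drug mean = (0.346 × -1.009 + 0.309 × 0.641) / 0.654 = -0.231.
- D = 0.497, giving 0.25 to 0.40 SD.

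| Share of reassuring skipped | 50% of controls reassuring | 70% of controls reassuring |
|---|---|---|
| 0 | 0.25–0.40 SD | 0.25–0.40 SD |
| 50% | 0.25–0.40 | 0.28–0.45 |
| 75% | 0.21–0.34 | 0.28–0.45 |
| 100% | 0.08–0.13 | 0.06–0.09 |

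Two-sided 5% power is 63 to 96% with full sampling and about 6 to 16% with all reassuring participants skipped. At half skipped, with 50% of controls reassuring, it is 48 to 86%; that loss comes from the smaller sample, not from bias.

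**RT-PCR.** Assume 60% of control and 75% of drug participants are reassuring, and RT-PCR is negative in 70% of reassuring and 30% of other participants in both arms.
- All sampled: 0.6 × 0.7 + 0.4 × 0.3 = 54%; 0.75 × 0.7 + 0.25 × 0.3 = 60%; +6 points.
- Half of reassuring skipped: 0.33/0.70 = 47.1%; 0.3375/0.625 = 54.0%; +6.9 points.
- All skipped: 30% against 30%; 0 points.
- If the drug also raises negativity to 40% among the non-reassuring, the true effect is +8.5 points and full omission gives +10.

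**Weighting.** In this model, reweighting by reassuring status gives, on drug, 0.691 × -1.009 + 0.309 × 0.641 = -0.50, the true mean. This works at any w below 1. At w = 1 there is no sampled reassuring participant to weight.

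**Laboratory events.** Take a true risk of 15% in both arms, unrelated to clinical course, with 50% and 65% reassuring and none of them sampled. Recorded over all treated: 0.15 × 0.50 = 7.5% against 0.15 × 0.35 = 5.3%. Over those sampled: 15% in both arms.

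**The case against.** The contingency is conditional, applies only to people reachable by telephone, protects D7 ahead of D14, and goes to the SAB. Undone visits will be described (section 6.3.2), and visits performed against visits foreseen are a process indicator (section 9.2.2). Remote visits still record undesired effects (section 5.3.5), so only laboratory-detected events are exposed, and section 6.3.7 names a between-arm comparison only for events tied to treatment discontinuation or dosage modification. The primary endpoint needs no sample and treats missing as failure. Section 6.3.1 leaves details of secondary endpoint analyses to the statistical analysis plan.

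This limits the reach of the point. It does not remove it, because the protocol itself fixes both the omission rule and the available-data handling, and none of these safeguards restores the comparison.

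A reader might go further and infer that real effects would always shrink toward zero, in proportion to the time the contingency is in force. The calculation does not support that: at half omission the estimate is about right or too large, and marked attenuation appears only at or near total omission. A reader might also infer that weighting cannot help. That is true only if no reassuring participant is sampled, which the text does not imply: replacement is optional, and full-visit periods would still sample them. Nor are those sampled simply the sickest, since hospitalised participants may miss home samples too.

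**Conclusion.** The concern holds for the D7 and D14 sample-based secondary endpoints and for laboratory adverse events, and only if the contingency is used. The stated rules would then give comparisons that no longer follow randomisation, with a bias whose size and direction depend on how many reassuring participants were skipped and on how the drug acts. Under the assumptions shown, a true 0.25 to 0.40 SD marker difference could be estimated anywhere from about 0.06 to about 0.45 SD. These figures illustrate the mechanism; they do not forecast the trial's result. The primary analysis is not touched. The point is worth correcting before recruitment, because the records needed for a repair may not be recoverable later.

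**What to change.** - **Section 5.3.9:** log the start and stop dates of any visit reduction. For each participant, record the reassuring and telephone status that led to omission.
- **Section 6.3.6:** analyse D7 and D14 sample-based endpoints with the inverse probability weighting already defined in section 6, using that recorded status and calendar period. Add a sensitivity analysis restricted to participants whose scheduled visit fell in a full-visit period, applied alike to all arms. If reduction is in force throughout, so that no reassuring participant is sampled, the restricted set is empty and weighting is impossible; report these endpoints descriptively, without between-arm inference.
- **Section 6.3.7:** give laboratory adverse event rates with the number actually sampled as denominator. This removes the dilution shown above; it does not remove selection if the event risk itself follows clinical course.

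Visit rules and participant care do not change. The cost is somewhat wider intervals, a date log, one recorded status per omitted visit, and a little extra analysis.

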### 3.2 Secondary objectives

The study's secondary objectives are:

- Appraise the efficacy of several experimental treatments of SARS-CoV-2 infection, compared with standard of care, to prevent death on Day 28
- Appraise the efficacy of several experimental treatments of SARS-CoV-2 infection, compared with standard of care, to prevent hospitalisation on Day 28
- Appraise the efficacy of several experimental treatments of SARS-CoV-2 infection, compared with standard of care, to prevent admission to intensive care unit on Day 28
- Appraise the efficacy of several experimental treatments of SARS-CoV-2 infection to eliminate nasopharyngeal carriage of the virus, compared with standard of care
- Appraise the efficacy of several experimental treatments of SARS-CoV-2 infection, compared with standard of care, to prevent loss of autonomy
- Appraise tolerance of experimental treatments against SARS-CoV-2 infection
- Study those factors associated with clinical deterioration in patients with COVID-19
- Evaluate the feasibility and acceptability of the trial and model of care model implemented.
- Evaluate the relationship between concentrations for each drug and efficacy of each of the treatments

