## 6 Statistical analysis

- Inclusion and exclusion from statistical analysis

Participants who died, were lost to follow-up or withdrew consent will be included in the analysis. Participants with at least one of the following conditions could be excluded:

- Having never taken trial treatment or ignoring the allocated arm
- Included without signing a consent form
- Included despite non-compliance with at least one major eligibility criterion
- Having withdrawn consent

The SAB will review cases documentation collected by the trial team and will take an exclusion decision blinded of the randomisation arm and the participant's post inclusion evolution.

Major deviations from eligibility criteria are defined as any deviation on the following criteria:

- Positive SARS-CoV-2 RT-PCR
- Age  $\geq$  65 years

Randomisation treatment discontinuation will be managed as follows:

- On intention to treat (ITT)  
Any participant will be analysed in the allocated arm, disregarding eligibility deviations or non-compliance with randomisation treatment.  
All data will be used.
- On treatment (OT)  
Any participant will be analysed in the allocated arm, irrespective of eligibility deviations or non-compliance with randomisation treatment.  
All data observed after discontinuation of randomisation treatment will be dropped.
- Per protocol (PP)  
Any participant will be analysed in the allocated arm, irrespective of minor eligibility deviations or minor non-compliance with randomisation treatment.  
All data from any participant with a major eligibility deviation or a major non-conformity with randomisation treatment will be dropped.
- As treated (AT)  
Any participant will be analysed with respect to the actually received treatment, irrespective of the allocated treatment.

Missing values will be managed as follows:

- Analysis on available data (AD): any missing value will be ignored.
- Missing as failure (M=F) procedure: any missing value will be analysed as a failure (main endpoint: disease worsening)
- Worst case procedure (WC):  
First sub-analysis: Any missing data is analysed as a success in the first arm, and as a failure in the second arm.  
Second sub-analysis: Any missing data is analysed as a failure in the first arm, and as a success in the second arm  
The conclusion will be that of each sub-analysis if they are identical.
- Inverse probability weight (ITW) procedure:  

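### If Day 14 swabs are omitted for Day 7 negatives, as section 5.3.9 allows, the available-data rule drops those people from the Day 14 reversion proportion and distorts that comparison

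*Protocol*

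**What the plan says.** The default schedule (Table 1, sections 5.3.6 and 5.3.10.1) swabs participants at Day 7 and Day 14. The results feed a secondary criterion in 4.3.2: "Proportion of patients with a reversion of SARS-CoV2 RT-PCR on a nasopharyngeal swab on Day 7 and Day 14, in each group". It serves the objective in 3.2 of assessing whether the treatments work "to eliminate nasopharyngeal carriage of the virus, compared with standard of care".

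Section 5.3.9 sets out how the schedule may be cut back if workload or shortages require it. Two of its options remove swabs:

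- "The nasopharyngeal tests of Day 14 could be omitted for people, who had tested negative on Day 7".
- Day 7 and Day 14 visits "could be replaced by remote visits for people available by telephone and whose changes are clinically reassuring". For these, "The corresponding samples would therefore be omitted".

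The section closes with a safeguard: "Potential changes to the schedule shall be strictly framed and submitted to the SAB".

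On analysis, 6.3.6 says: "The analyses on the secondary endpoints will be performed on intention-to-treat on available data, except for safety analysis". Section 6 gives the meaning of that term: "Analysis on available data (AD): any missing value will be ignored". Nowhere does the protocol say that someone negative at Day 7 whose Day 14 swab was skipped counts as negative at Day 14.

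**The concern.** Each rule is reasonable alone. Skipping a repeat swab in someone already negative saves scarce tests, and available-data analysis is a common default for secondary endpoints. Together they make the existence of a Day 14 value depend on the Day 7 result. That result is a post-randomisation outcome which the antiviral arms are meant to change. Ignoring the missing values then conditions the Day 14 comparison on response to treatment. The arm that clears virus faster loses more of its successes from numerator and denominator, and the groups compared are no longer those formed by randomisation.

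At stake is the Day 14 half of the trial's virological efficacy criterion.

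**Working it through.** **Inputs.** The protocol gives no clearance rate, power or alpha for the swab endpoint, so there is no stated figure to reproduce. From the protocol: 169 participants per arm in the main stratum (6.2.1), 1:1 allocation (4.2), and the rules above. Assumed: all clearance rates, no return to positive between Day 7 and Day 14, and a two-sided 0.05 test where power is quoted.

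**Formula.** Let p7 and p14 be the true proportions negative at Day 7 and Day 14, and f the fraction of Day 7 negatives whose Day 14 swab is omitted. The available-data proportion at Day 14 is

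[(p14 − p7) + p7(1 − f)] / [(1 − p7) + p7(1 − f)].

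With f = 1 this is (p14 − p7)/(1 − p7), the conversion rate among people still positive at Day 7. It cannot exceed p14, because p14 − p7 ≤ p14(1 − p7) whenever p14 ≤ 1. So clearance is understated in both arms.

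**Main illustration.** Assume 40% (control) and 60% (experimental) negative at Day 7, and that 60% of the remaining positives clear by Day 14 in both arms, meaning no drug effect after Day 7.

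- True Day 14, control: 0.40 + 0.60 × 0.60 = 0.76.
- True Day 14, experimental: 0.60 + 0.40 × 0.60 = 0.84. True difference: +8 points.
- Full omission, control: 0.36/0.60 = 0.60. Experimental: 0.24/0.40 = 0.60. Observed difference: 0. The arms are understated by 16 and 24 points.
- Half omission, control: (0.36 + 0.20)/(0.60 + 0.20) = 0.70. Experimental: (0.24 + 0.30)/(0.40 + 0.30) = 0.771. Observed difference: +7.1 points.

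**Range, 169 per arm.** The first two columns give the assumed percentages negative at Day 7/Day 14. In the hazard-ratio rows the drug acts throughout, the clearance hazard is constant, and control clearance at Day 7 runs from 20% to 40%.

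| Control | Experimental | Omitted | True difference (points) | Observed difference (points) | Power, complete data to observed |
|---|---|---|---|---|---|
| 30/60 | 50/75 | all | +15.0 | +7.1 | 84% to 17% |
| 30/60 | 50/71.4 | all | +11.4 | 0 | 60% to none beyond chance |
| 30/60 | 50/70 | all | +10.0 | −2.9 | 49% to 6% |
| 20/50 | 40/65 | all | +15.0 | +4.2 | 80% to 10% |
| Hazard ratio 1.5 | | all | +12.8 to +14.7 | +8.4 to +13.5 | 66–84% to 35–44% |
| Hazard ratio 2 | | all | +23 to +25 | +16 to +24 | 99–100% to 80–86% |
| 30/60 | 50/71.4 | half | +11.4 | +9.0 | 60% to 32% |

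The retained groups are also unequal. In the first three rows about 118 controls (169 × 0.70) and 84 experimental participants (169 × 0.50) keep a Day 14 value.

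Attenuation is usual but not universal. At hazard ratio 2 with 40% control clearance at Day 7, full omission shows +24.0 against a true +23.0. With half omitted, that case shows +25.9, and hazard ratio 1.5 at the same control rate shows +15.5 against +14.4. Power still falls in all of these.

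**Day 7.** Omission is decided after the Day 7 swab, so it cannot alter that comparison. The main illustration still shows 40% versus 60% there.

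**The case against.** Several points on the other side stand.

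- **It is a contingency.** Everyone is swabbed by default, and changes go to the Scientific Advisory Board. The bias arises only if the option is used. But the option is written in advance because shortages were foreseen, and the board's review concerns the schedule. Nothing in 5.3.9 alters the analysis rule.
- **The full-omission figures are an extreme.** A reader might infer that the Day 14 comparison keeps only slow clearers. That is exact only if every Day 7 negative is skipped, and the text says only that swabs could be omitted. The vanishing difference further needs no drug effect after Day 7, although dosing runs to Day 9.
- **An early effect would still show.** A reader might infer that the plan would hide an antiviral effect altogether. It would not: the omission rule leaves the Day 7 half of the criterion intact, and 5.3.9 gives Day 7 visits priority.
- **The details belong to the SAP.** Section 6.3.1 does defer details of secondary analyses. This is more than a silence, though: 6.3.6 and section 6 state a rule, and it gives the wrong result when combined with 5.3.9. Worst-case and inverse-probability-weighted variants are named in 6.3.4 only for the primary endpoint.

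The remote-visit option also removes swabs, including at Day 7, from people who are clinically reassuring, and the trial is open-label. It is tempting to say this biases in the same direction. The documents do not establish that: they make no stated swab provision for people who are hospitalised or die, so the net direction is unknown.

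**Conclusion.** The point holds conditionally. If the Day 14 omission in 5.3.9 is used, the stated available-data rule makes the Day 14 reversion proportion a comparison selected on treatment response and understates clearance in both arms. Under the assumed rates with full omission, the difference runs from little changed (hazard ratio 2) through roughly halved (+15 to +7 points) to zero or slightly reversed. With half of Day 7 negatives omitted the loss is milder (+11.4 to +9.0 points), but power still falls from 60% to 32%.

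These sizes rest on assumed clearance rates and on no return to positive; the direction for each arm's own proportion rests only on the latter. One secondary criterion at one time point is affected. The primary endpoint of hospitalisation or death is not touched.

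**What to change.** 1. In 4.3.2, define reversion at Day 14 as a negative Day 14 swab, or a negative Day 7 swab where the Day 14 swab was omitted under 5.3.9.
2. In 6.3.6, state that these participants stay in the Day 14 denominator as reverted and are not treated as missing.
3. Report omitted swabs by arm and reason, separating Day 7 negatives from visits made remote because the person was clinically reassuring. For the remote-visit losses add a sensitivity analysis, for example the inverse probability weighting already defined in section 6.

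The cost is a few sentences, one reason field for each omitted swab and one sensitivity analysis. No extra swabs are needed and patient care does not change.

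The downside is the assumption that nobody negative at Day 7 is positive again at Day 14. If a fraction q of them were, full omission would overstate each arm by q × p7. In the main illustration the difference would be overstated by q × (0.60 − 0.40) = 0.20q. That assumption should be stated beside the definition.
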